#### The ‘learning curve’ population

The EuroHYP-1 trial is a very large and complex trial with multiple nations and sites investigating a complex intervention. To account for this, we define a ‘learning curve’ analysis set, where we will analyse independently the first five participants included at each centre and compare those results to the results of all participants minus the first five.

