
### The sample size

Originally, we planned to demonstrate or reject an absolute difference of 7% between the intervention groups (equivalent to an odds ratio (OR) of 0.74) and allowing for 3% loss to follow up in a sample size of 1500 randomised patients with a type 1 error risk of 5% and a type 2 error risk of 10% (EuroHYP-1, EudraCT number 2012-002944-25, version 2, 20 December 2012). Due to exceptionally slow enrolment, we realised that this target was no longer realistic. Accordingly, in 2014, the sample size was downgraded to 800 patients based on considerations explained in version 4 of the protocol (EuroHYP-1, EudraCT number 2012-002944-25, European Database on Medical Devices (EUDAMED) number CIV-12-09-008821, planned trial period July 2013 to March 2017 (45 months), version 4, date 29 June 2015). Currently, the project has been prolonged until 31 July 2018.

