### Adjusting variables

The randomisation is stratified according to the nationality of the participating centres and, within each stratum, the patient allocation is based on probabilistic minimisation (80:20) using the following factors:Intention to perform thrombolysis (yes compared to no).Method of cooling (surface compared to endovascular).Sex (male compared to female).Stroke severity (National Institutes of Health Stroke Score (NIHSS)) 6–12 compared to 13 or higher).Age (≤ 65 years compared to > 65 years).Visibility of a relevant ischaemic lesion on the first brain imaging (yes compared to no).Time since symptom onset (≤ 4 hours compared to 4–6 hours).

The primary analyses will be adjusted by the protocol-specified stratification variable country and the seven minimisation factors.

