#### Subgroup analysis

The duration of the cooling intervention was reduced from 24 hours to 12 hours after the recruitment of 50 participants. To investigate this protocol change, we will conduct a subgroup analysis for the primary and secondary outcomes. In the analysis, we will compare the participants who were included before the protocol change to participants included after the protocol change.

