#### Sensitivity analyses

The analyses of the primary and secondary outcomes will be repeated using the per protocol population and the ‘learning curve’ population.

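### The learning-curve comparison may be partly confounded with the change from 24-hour to 12-hour cooling, to a degree the plan does not let one judge, and it has no test of whether the treatment effect differs

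*SAP article*

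**What the plan says.** The section on the 'learning curve' population in the SAP article says the trial will "analyse independently the first five participants included at each centre and compare those results to the results of all participants minus the first five". The Sensitivity analyses section gives this set its role: "The analyses of the primary and secondary outcomes will be repeated using the per protocol population and the ‘learning curve’ population".

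The Subgroup analysis section records a change of intervention during the trial: "The duration of the cooling intervention was reduced from 24 hours to 12 hours after the recruitment of 50 participants". It plans a separate analysis of that change, in which "we will compare the participants who were included before the protocol change to participants included after the protocol change".

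On adjustment, the Adjusting variables section says: "The primary analyses will be adjusted by the protocol-specified stratification variable country and the seven minimisation factors". Cooling duration and protocol period are not on that list. None of these sections says that the learning-curve analysis takes account of the duration change, or the reverse.

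**The concern.** A learning-curve analysis asks whether the effect of cooling differs between a centre's early and later participants. Here early at the centre and early in the trial overlap, and early in the trial also means allocation under the 24-hour schedule. If 24-hour and 12-hour cooling differ in effect, the first-five set can carry more of the 24-hour effect than the remainder does. Part of an apparent learning effect could then be a duration effect, or a duration effect could mask real learning. Randomisation protects the comparison of arms within each set. It does not protect the comparison between the sets, which is what this analysis is for.

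The form of the comparison is a second weakness, and it does not depend on centre counts. The two sets are analysed separately and their results set side by side, with no stated test of whether the treatment effect differs. A small first-five set can give a non-significant result, and the larger remainder a significant one, with no difference in effect between them.

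**Working it through.** The plan gives no figure for the overlap of the two splits, so there is none to reproduce. The check asks how large the overlap, and the bias from it, could be.

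**Inputs from the SAP article.** Total N = 800 (The sample size). 24-hour-era participants = 50, both arms together (Subgroup analysis). First-five rule, k = 5 per centre ('learning curve' population). Odds ratio 0.74 (The sample size), borrowed only to scale a possible difference between 24-hour and 12-hour cooling.

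**Assumed, because not given.** The number of centres active for the first 50 (3 to 30), the total number of centres C (10 to 80), and at least five participants at every centre. The article says only that this is "a very large and complex trial with multiple nations and sites".

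**Step 1: how many of the first 50 are among their centre's first five (m).** With c centres sharing the 50 evenly, m = min(50, 5c). For uneven recruitment, the 50 were divided at random with Dirichlet(1) centre weights (4,000 runs).

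| Centres active for the first 50 | Even split, m/50 | Uneven split, mean m/50 |
|---|---|---|
| 3 | 30% | 27% |
| 5 | 50% | 40% |
| 8 | 80% | 55% |
| 10 | 100% | 62% |
| 20 | 100% | 83% |
| 30 | 100% | 92% |

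**Step 2: share of 24-hour-era participants in each set.** First-five set: p1 = m/(5C). Remainder: p2 = (50 − m)/(800 − 5C). Their overall share is 50/800 = 6.25%, so they are over-represented in the first-five set when m/(5C) > 0.0625, that is m > 0.3125 × C. This needs m of 7 or more with 20 centres and 13 or more with 40. With 80 centres and m = 25 the two shares are equal (25/400 = 25/400).

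**Step 3: size of the leak.** If 24-hour rather than 12-hour cooling multiplied the treatment odds ratio by 0.74, the spurious ratio of odds ratios (first five over later) is about 0.74^(p1 − p2). The standard error of the difference in log odds ratios is about √[12/(0.97 × 5C) + 12/(0.97 × (800 − 5C))]. This is the usual variance for an ordinal outcome with 1:1 allocation. The factor 0.97 is an assumption about the spread over the mRS categories.

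| C | p1, full overlap (m = 50; p2 = 0) | Spurious ratio, m = 50 | SE of log ratio | Leak in SE, m = 50 | Spurious ratio, m = 15 |
|---|---|---|---|---|---|
| 10 | 100% | 0.74 | 0.514 | 0.59 | 0.93 |
| 20 | 50% | 0.86 | 0.376 | 0.40 | 0.97 |
| 40 | 25% | 0.93 | 0.287 | 0.26 | 1.00 |
| 60 | 17% | 0.95 | 0.257 | 0.20 | 1.01 |
| 80 | 12.5% | 0.96 | 0.249 | 0.15 | 1.02 |

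For example, with C = 20 and m = 50: 0.74^0.5 = 0.86, and 0.5 × |ln 0.74| / 0.376 = 0.151/0.376 = 0.40.

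**Step 4: does the planned before/after analysis separate the two?** It has the mirror-image overlap. With C = 20 and m = 50, every participant before the change is a first-five participant, against (100 − 50)/750 = 6.7% after it. With m = 15 the shares are 15/50 = 30% and (100 − 15)/750 = 11.3%. Two marginal contrasts that overlap in this way cannot, side by side, show which factor is at work. That takes both factors in one model, or restriction to one period.

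**The case against.** A reader might infer more than the article supports, in three ways.

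- **That the first 50 fall mainly among their centres' first five.** The article gives no centre count and no distribution of the 50. Slow enrolment, which it mentions when explaining the reduced sample size, fits a few active centres as well as many slow ones. Step 1 shows that a majority needs more than 5 active centres with even recruitment and about 8 with uneven recruitment.
- **That the comparison cannot be interpreted.** The largest shares in Step 3 assume complete overlap. Even then, with 40 or more centres at least 75% of the first-five set was recruited under the 12-hour schedule. With 20 to 80 centres the leak is 0.15 to 0.40 standard errors, small beside the imprecision of the contrast itself: the 95% confidence limits lie a factor of about 2.1 (20 centres) to 1.6 (80 centres) either side of the estimate.
- **That a duration effect would be taken for learning.** The plan names the duration change and schedules its own analysis for the same outcomes, so a reader would see both.

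It also stands that this is a sensitivity analysis. It is outside the fixed testing sequence and has no row in the table shells. The arm comparison within each set stays valid, and the result without the first five still shows whether the main finding holds without early participants. One may add that an article can leave the form of the comparison to a fuller plan, and that the text does not rule out an interaction test.

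These arguments limit the size of the concern but do not remove it. The overlap is built into the two definitions, nothing in the described analysis deals with it, and the separate before/after analysis shares it.

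**Conclusion.** The concern holds as a possibility of partial confounding. Both splits follow calendar time, and the learning-curve comparison is neither adjusted for protocol period nor restricted by it. The degree runs from negligible (few early centres, many centres in total) to substantial (about ten centres, all 50 among the first five). The article does not allow a choice within that range. The bias figures rest on the assumed centre counts, on at least five participants per centre, and on an illustrative duration effect of 0.74 for which the article offers no evidence. Separately, the comparison of two sets of results lacks a test of difference in treatment effect, whatever the centre counts. No primary or confirmatory conclusion depends on this analysis, so it is a minor point.

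**What to change.** Keep the first-five definition and the planned analysis, and add to the Sensitivity analyses section:

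1. Test learning as the arm by (first five versus later) interaction in the adjusted intention-to-treat model, and report the treatment effect within each set with its 95% confidence interval.
2. As a supporting analysis, repeat this either with a protocol-period indicator and its interaction with arm, or only in participants randomised after the change, each keeping their true order number at the centre.
3. Report how many first-five participants come from each period, so that the overlap can be seen.

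The cost is SAP wording and a little analysis work. The supporting analysis loses precision, and most where the overlap is greatest. Under full overlap, restriction removes half of the first-five set with 20 centres and all of it with 10, and those removed are the earliest participants at the earliest centres. The period-indicator version meets the same limit, because under full overlap learning is then estimated only from first-five participants recruited after the change. If few centres opened after the change, it will say little or nothing about learning. For that reason it should be added to the planned analysis and not replace it.

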**Methods/design:**

The EuroHYP-1 trial is a multinational, randomised, superiority phase III clinical trial with masked outcome assessment testing the benefits and harms of therapeutic cooling in awake adult patients with acute ischaemic stroke. The outcomes dealt with here include the *primary outcome* the Rankin score (mRS) at day 91 +/-14 days after randomisation. The *secondary and exploratory outcomes* at day 91 +/-14 days unless otherwise stated encompassing: (1) death or dependency, defined as mRS score > 2; (2) death; (3) National Institutes of Health Stroke Score; (4) brain infarct size at 48 +/-24 hours; (5) EQ-5D-5 L score, and (6) WHODAS 2.0 score. Other outcomes are: the *primary safety outcome* serious adverse events; and the incremental cost-effectiveness, and cost utility ratios. The *analysis sets* include (1) the intention-to-treat population, and (2) the per protocol population. The sample size is estimated to 800 patients (5% type 1 and 20% type 2 errors). All analyses are adjusted for the protocol-specified stratification variables (nationality of centre), and the minimisation variables. In the analysis, we use ordinal regression (the primary outcome), logistic regression (binary outcomes), general linear model (continuous outcomes), and the Poisson or negative binomial model (rate outcomes).

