### Statistical analyses

#### Analytical principles

Analyses will be conducted according to the intention-to-treat principle [2] if not otherwise stated.

All primary tests of significance will be two-sided with alpha = 5%. Analyses will be conducted blinded with the two intervention groups coded as, e.g. 0 and 1. Two conclusions will be drawn, one assuming 0 is the intervention group and 1 is the control, and one assuming the opposite. After two abstracts with two conclusions have been written and both accepted by the Steering Group, the code will be broken.

The primary analyses of primary, secondary, and exploratory outcomes will be those of the intention-to-treat population adjusted for the protocol-specified stratification variable and the minimisation variables, and if necessary using data sets generated using multiple imputation.

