#### Power of the original secondary outcomes

As the sample size is based on the primary outcome, we have calculated the power of each of the originally planned secondary outcomes given the sample size of 800 patients.

Death day 91 ± 14 days after randomisation: the implied clinically relevant minimal change in mortality that needs to be detected may be calculated based on (1) the mortality of 17% found in the meta-analysis quoted in the protocol [1]; (2) the assumption that wherever the mRS is dichotomised, the odds ratio for treatment versus control will be the same, the ‘common odds ratio’; and (3) the requirement that this common odds ratio should not be larger than 0.74 (see the sample size calculation). Let the unknown change in mortality in the experimental group be x. If we assume the OR for the dichotomy mRS > 5 compared to mRS ≤ 5 will be 0.74 and the mortality of the control group is 17% as quoted in the meta-analysis, we may find x by solving the equation OR = ((0.17–x)/(0.83 + x))/(0.17/0.83) = 0.74 to obtain x = 0.0384 giving a mortality of 0.1700 – 0.0384 = 0.1316 in the cooled patients versus 0.1700 in the controls. Using a sample size of 800 participants, the power is found to be 0.33.

Death or dependency (mRS > 2) 91 ± 14 days after randomisation: using the same reasoning, the power of this outcome can be calculated by solving the equation (0.63–x)/(0.37 + x))/0.63/0.37 = (0.63 – x)0.63/(0.37 + x)0.37 = 0.74 as 63% of the patients in the meta-analysis had mRS > 2 implying x = 0.0725. The power may then be calculated to be 0.55.

NIHSS score 91 ± 14 days after randomisation: assuming a minimal relevant difference of 2 points, a standard deviation (SD) of 5 points [5], an α of 0.05, and a sample size of 800 participants, the power may then be calculated to 1.00.

EQ-5D-5 L score 91 ± 14 days after randomisation: assuming a minimal relevant difference of 0.05 points, a SD of 0.40 points [6–9], an α of 0.05, and a sample size of 800 participants, the power may then be calculated to 0.42.

WHODAS 2.0 score 91 ± 14 days after randomisation: we originally planned to analyse the World Health Organization Disability Assessment Schedule II (WHODAS 2.0) score at outcome assessment in the period day 91 ± 14 days after randomisation. However, due to difficulties in assessing the clinical meaning, we are not able to calculate the power, and we will thus analyse this as an exploratory outcome.

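### The learning-curve analysis compares two separately analysed subsets without any estimate, test or interval for the difference in treatment effect between them

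*SAP article*

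**What the plan says.** Under 'The learning curve population', the SAP article defines an analysis set to allow for the complexity of the intervention and the number of sites. It will "analyse independently the first five participants included at each centre and compare those results to the results of all participants" other than those five. Under 'Sensitivity analyses' this is applied broadly: "The analyses of the primary and secondary outcomes will be repeated using the per protocol population and the ‘learning curve’ population".

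No other section says how the two sets of results are to be compared. 'Multiplicity' covers the order of the confirmatory tests. 'Subgroup analysis' concerns the change in cooling duration. 'Analysis of the primary and the secondary outcome' gives the models for the treatment comparison: ordinal regression with a van Elteren fallback, logistic regression, the general linear model, and Poisson or negative binomial models. None of these carries a term for early versus later participants. The only interaction written out in the article is treatment by time, in the exploratory temperature model.

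**The concern.** The question behind this analysis is whether the effect of cooling differs between a centre's first five participants and its later ones. That is a question about a difference between two effects. Two separate analyses, each set against no effect, do not answer it. The difference needs its own estimate and its own uncertainty.

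Without these, the reader has two estimates and two p values. Five participants per centre reach half of 800 only with 80 full centres, so the early subset is probably the smaller one. A non-significant early result beside a significant later one is then a common outcome even when the effect is constant, and it is just the pattern that a learning curve would produce. At stake is a spurious statement in the main publication that centres had to learn, or that early patients diluted the result.

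**Working it through.** **Inputs from the SAP article.**
- Test level ('Analytical principles'): "All primary tests of significance will be two-sided with alpha = 5"%.
- Size and power (abstract, 'Methods/design'): "The sample size is estimated to 800 patients (5% type 1 and 20% type 2 errors").
- Common odds ratio ('Power of the original secondary outcomes'): "the requirement that this common odds ratio should not be larger than 0.74".
- Death or dependency (same section): "63% of the patients in the meta-analysis had mRS > 2 implying x = 0.0725", so 63% versus 55.75%.
- Death (same section): 17.00% versus 13.16%.

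**Assumptions.** Equal arms; 10 to 80 centres, each contributing a full five early participants (50 to 400 early participants); information proportional to subset size.

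**The plan's own figures.** With n = 400 per arm, power = Φ{[|p1 − p2| − 1.96 √(2p̄(1 − p̄)/n)] / √[(p1(1 − p1) + p2(1 − p2))/n]}.
- mRS > 2: p̄ = 0.59375, so Φ[(0.0725 − 1.96 × 0.03473)/0.03463] = 0.551. The article gives 0.55.
- Death: 0.329. The article gives 0.33.

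**Primary outcome, same true effect in both subsets.** The article prints no full mRS distribution, so the calculation starts from the stated power. For 80% power at N = 800 the expected z statistic is θ = 1.960 + 0.842 = 2.802. A subset with share f of the patients has expected z of θ√f and power Φ(θ√f − 1.96) + Φ(−θ√f − 1.96).

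For 150 early and 650 later participants:
- Early: f = 150/800 = 0.1875, θ√f = 1.213, power 0.228.
- Later: f = 650/800 = 0.8125, θ√f = 2.525, power 0.714.
- Later only significant: 0.772 × 0.714 = 0.551.
- Early only significant: 0.228 × 0.286 = 0.065.
- Exactly one significant: 0.551 + 0.065 = 0.616.

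| Assumed centres | Early / later | Power early | Power later | Exactly one significant |
|---|---|---|---|---|
| 10 | 50 / 750 | 0.108 | 0.774 | 0.715 |
| 20 | 100 / 700 | 0.168 | 0.746 | 0.663 |
| 30 | 150 / 650 | 0.228 | 0.714 | 0.616 |
| 40 | 200 / 600 | 0.288 | 0.679 | 0.576 |
| 60 | 300 / 500 | 0.404 | 0.601 | 0.519 |
| 80 | 400 / 400 | 0.508 | 0.508 | 0.500 |

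**Two secondary outcomes**, from the article's own proportions over the same range of centres: exactly one subset is significant in 43% to 52% of trials for mRS > 2 and in 31% to 34% for death.

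**No effect of cooling at all:** 2 × 0.05 × 0.95 = 0.095.

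**What an interaction test would do.** With a constant effect it would be falsely positive in 5% of trials per outcome. Its power is low. Suppose cooling did nothing in the first five and had the planned effect later. The expected z for the interaction is then θ√(f(1 − f)):
- 50/750: 2.802 × √(0.0625 × 0.9375) = 0.678, power about 0.10.
- 150/650: 2.802 × √(0.1875 × 0.8125) = 1.093, power about 0.19.
- 400/400: 2.802 × 0.5 = 1.401, power about 0.29.

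**The case against.** The strongest objection is that the article never says significance will be compared. Its wording fits a comparison of estimates equally well, and every discordance figure above applies only if the comparison is made on significance. A reader might infer that the plan will declare a learning curve whenever one subset is significant and the other is not. The text does not support that. What stands is narrower: under either reading, no measure of uncertainty for the difference is fixed.

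A second objection is that a condensed article may leave such detail to a fuller document. This has limited force, because the article does state a method (separate analyses, then a comparison), and it is the method that is weak.

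Third, nothing confirmatory depends on this. It is a sensitivity analysis, the adjusted intention-to-treat analysis remains primary, and the comparison is outside the fixed testing sequence. A reader might infer that the trial's error rate or main conclusion is at risk; neither is. Because the subsets do not overlap, a reader could also derive the difference and an approximate interval from two reported estimates with standard errors. All of this stands and keeps the point minor.

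Finally, an interaction test would rarely detect a real learning curve, as the power figures show. That is true. It is a reason to report the interval, which shows how little the data can say, where two p values would hide it.

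**Conclusion.** The concern holds as a minor point of analysis choice. The article plans separate analyses and a comparison, with no estimate, test or interval for the quantity in question. If the comparison were made on significance, a constant effect at the planned size would give one significant and one non-significant mRS result in about half to nearly three quarters of trials (50% to 72%), and in about 62% with a 150/650 split. Those figures rest on the stated 80% power at 800, equal arms, an assumed 10 to 80 centres and five early participants at each. They do not depend on an assumed mRS distribution. The primary result and its type 1 error are unaffected.

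**What to change.** For the learning-curve sensitivity analysis, replace the two separate fits by one model per outcome on all intention-to-treat participants. It should hold treatment, the planned adjustment variables (country and the seven minimisation factors), an indicator for the first five at the centre, and the treatment-by-indicator interaction. Report the two subset effects and their ratio (odds ratios) or difference (continuous outcomes) with a 95% CI. State that any remark about a learning curve will rest on that interval and not on the two subset p values.

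If proportional odds is rejected and the van Elteren fallback applies, there is no interaction term to fit. Name an effect estimate for each subset in advance and report the difference between the two with its CI.

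Two cautions belong in the text. The interaction has low power, so a wide interval is inconclusive and does not show that there was no learning curve. Early status at a centre may also overlap with the change in cooling duration after 50 participants ('Subgroup analysis'), so a difference could not be put down to experience alone.

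The cost is a few sentences in the SAP and two added terms per model. No new data are needed.
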